# Tranexamic Acid for reduction of intra- and postoperative TRansfusion requirements in elective Abdominal surgery (TATRA): study protocol for an investigator-initiated, multicenter, double-blind, placebo-controlled, randomized superiority trial with two parallel groups

**DOI:** 10.1186/s13063-024-08541-8

**Published:** 2024-10-19

**Keywords:** Tranexamic acid, Abdominal surgery, Perioperative bleeding, Blood transfusion, Patient blood management

## Abstract

**Background:**

Intra- and postoperative hemorrhage is a relevant problem in major abdominal surgery, leading to acute anemia and necessitating transfusion of packed red blood cells. It is estimated that in 30% of abdominal surgeries, intra- or postoperative transfusion is required. Transfusion potentially has detrimental health effects and poses a considerable socioeconomic burden. Tranexamic acid, a lysine analog inhibiting plasminogen activation and providing clot stability, has been used to reduce hemorrhage. While there is ample evidence in other surgical disciplines, it is almost completely lacking in abdominal surgery.

**Methods:**

This multicenter double-blind parallel group randomized superiority trial will compare tranexamic acid (loading dose 1000 mg over 10 min prior to skin incision, maintenance dose 125 mg/h continuously until skin closure or until 1000 mg have been administered) to placebo in patients ≥ 18 years undergoing elective esophagectomy, gastrectomy, colectomy, rectal resection, pancreatic resection, or hepatectomy. The primary efficacy endpoint is the intra- or postoperative transfusion of at least one unit of packed red blood cells. Key secondary endpoints are the number of transfused units per patient, estimated intraoperative blood loss, postoperative complications/mortality, length of hospital stay, operation/anesthesia time, D-dimer levels, and quality of life. Sample size calculation is based on the assumption that in the control group, 30% of patients require transfusion while the intervention achieves a risk reduction of 33%, reducing the probability to 20%. With a type one error of 5% and a power of 90%, using a two-sided *χ*^2^ test, this results in 412 patients per group. Accounting for non-compliance, 425 patients are to be randomized per group. The total trial duration will be 30 months with a recruitment period of 18 months.

**Discussion:**

If the proposed trial yielded positive results, the routine use of tranexamic acid in major abdominal surgery would be supported. This would avoid acute anemia with detrimental effects such as tissue hypoxia and organ injury, as well as the negative immediate and delayed effects of transfusions.

**Trial registration:**

EU CT Nr: 2023–509970-43–01, NCT06414031. Registered on 10 May 2024.

**Supplementary Information:**

The online version contains supplementary material available at 10.1186/s13063-024-08541-8.

## Introduction

### Background and rationale {6a}

Despite many preventive efforts, intra- and postoperative hemorrhage still constitutes a relevant problem in major abdominal surgery, requiring perioperative transfusion of packed red blood cells (PRBCs) in about 30% of abdominal resections [1]. In hepatic surgery, perioperative mortality is attributed to intra- and postoperative hemorrhage in about 6% of fatalities [2]. For gastrectomy and esophagectomy, postoperative hemorrhage occurs in up to 5% of patients and bears a failure to rescue of up to 30% [2, 3]. Intra- and postoperative hemorrhage and the subsequent transfusion requirement have a relevant socioeconomic burden. The direct cost for transfusing one unit of PRBCs in Germany is estimated at 147 Euros [4]. Moreover, blood loss is associated with increased postoperative morbidity and length of hospital stay, which leads to substantial indirect costs. Transfusion itself can negatively affect the health of transfused patients. Both immediate effects such as allergic reaction, hemolysis, volume and potassium overload, and long-term sequelae such as alloimmunization or immunomodulatory effects, which are supposed to increase the risk of cancer recurrence in oncological patients, have been reported. Whereas immediate effects occur in 5–10% of transfused patients, the increase of the odds for cancer recurrence has been estimated for example for colorectal cancer to be 40–60% [5]. A higher mortality of patients who received blood transfusions has been found in observational studies [6]. These considerations have led to the multidisciplinary concept of “patient blood management” which aims at limiting the need for allogeneic blood transfusion in all at-risk patients with the aim of improving their clinical outcomes [7].

Tranexamic acid (TXA), a lysine analogue inhibiting plasminogen activation and providing clot stability, has been used to reduce hemorrhage. There is ample evidence from randomized controlled trials (RCTs) and meta-analyses that TXA use is associated with reduced blood loss in orthopedic [8–11], cardiac [12], urological [13], and gynecological surgery [14]. For example, an RCT showed that the probability of being transfused PRBCs after surgery for hip fracture experienced a relative reduction of 22% [15]. While a meta-analysis comprising 104 RCTs on all surgical interventions found a 34% relative reduction in blood loss with only small differences between different operations [16], another meta-analysis of 129 RCTs demonstrated a 38% lower transfusion probability in patients who received TXA [17]. A systematic review and meta-analysis comprising 216 RCTs comparing TXA to placebo or no treatment showed a significant decrease in overall bleeding mortality with no increase in the risk of thromboembolic events as the main adverse event of concern [18]. The hitherto largest RCT including 9.535 patients undergoing non-cardiac surgery showed a 2.6% lower risk for a composite outcome of bleeding in patients receiving TXA. Subgroup results for abdominal surgery were however not presented [19].

There are few trials evaluating the specific effect of TXA administration in abdominal surgery. Four trials were conducted in patients undergoing liver transplantation and one in patients undergoing elective liver resection. While three trials showed a significantly lower blood loss and transfusion requirement for TXA [20–22], two underpowered trials failed to show a difference [23, 24]. In a retrospective series of patients undergoing resection of colorectal liver metastases, a 41% reduction in transfusion probability was found following TXA administration [25], whereas another retrospective series showed no differences in hemoglobin drop and transfusion probability [26]. One RCT on TXA use in pancreatoduodenectomy failed to show a reduction in estimated blood loss [27]. Ongoing RCTs on the use of TXA in abdominal surgery without available results comprise TXA application in cytoreductive surgery (NCT03646474), colorectal cancer surgery (NCT03606785), liver resections (NCT02261415), and bariatric sleeve gastrectomy (NL8029).

In summary, while there is high-level evidence that administration of TXA reduces bleeding and transfusion requirements in several surgical sub-disciplines, specific evidence for major abdominal surgery, i.e., esophagectomy, gastrectomy, colectomy, rectal resection, pancreatic resection, and hepatectomy, is lacking. To provide such high-level evidence, a confirmatory RCT is warranted.

### Objectives {7}

The primary objective of this trial is to assess whether intraoperative administration of TXA reduces hemorrhage and thus the need for intra- and postoperative transfusion of PRBCs for major abdominal operations.

The secondary objectives are to measure the effect of TXA administration on the number of transfused units of PRBCs, on the timing of possible transfusions, on the amount of intraoperative blood loss, on the operation and anesthesia time, on the blood markers hemoglobin and D-dimers and on quality of life of participants. Moreover, the safety of perioperative TXA administration is to be assessed.

### Trial design {8}

This trial has a multicenter, double-blind, placebo-controlled, 1:1 ratio parallel-group, randomized superiority design. It represents a low-intervention clinical trial according to Clinical Trials Regulation (EU) 536/2014.

## Methods: participants, interventions, and outcomes

### Study setting {9}

The study is conducted at eleven academic hospitals in Germany. A list of all currently enrolled centers can be obtained on the European Medicines Agency website and at ClinicalTrials.gov.

### Eligibility criteria {10}

#### Inclusion criteria

Age 18 years or abovePlanned elective esophagectomy, gastrectomy, colectomy, rectal resection, pancreatic resection, or hepatectomyAdequate renal function with serum creatinine < 250 µmol/L (2.82 mg/dL)Written informed consent obtained before randomizationNegative pregnancy test for women of childbearing potential within 14 days of commencing study treatment. Females of reproductive potential must agree to practice highly effective contraceptive measures during the study. These comprise measures with a failure rate of < 1% per year when used consistently and correctly, such as intravaginal and transdermal combined (estrogen and progestogen containing) hormonal contraception, injectable and implantable progestogen-only hormonal contraception, intrauterine device, intrauterine hormone-releasing system, bilateral tubal occlusion; vasectomized partner, sexual abstinence (defined as refraining from heterosexual intercourse during the entire study period).

#### Exclusion criteria

Severe anemia, defined as a hemoglobin concentration < 8 g/dL (< 5 mmol/L) or anemia with hemoglobin concentration ≥ 8 to < 10 g/dL (≥ 5.0 < to < 6.2 mmol/l) and one or several of the following symptoms suggesting hypoxemia:Clinical signs of tachycardia, e.g., resting heart rate > 100 beats/min, palpitation, etc.Clinical signs of hypotension, e.g., resting systolic blood pressure < 100 mmHg, orthostatic dysregulation, etc.Clinical signs of dyspnea, e.g., speech dyspnea, resting respiratory rate > 20 breaths/min.Thrombocytopenia with platelets < 60 × 109/LConfirmed bleeding disorder with the need for specific preventive perioperative treatment (e.g., factor deficiency with the need for perioperative substitution)A priori refusal of blood transfusionsConfirmed thrombophilia with a pertinent need for perioperative anticoagulationAllergy/hypersensitivity to TXARecent (< 30 days) thromboembolic eventHistory of medically confirmed convulsionsIn female subjects: pregnancy or lactation.

All participating study centers are institutions with a vast experience in conducting larger abdominal surgery comprising esophagectomy, gastrectomy, colectomy, rectal resection, pancreatic resection, and hepatectomy. All study sites need to fulfill GCP requirements.

### Who will take informed consent? {26a}

During visits to discuss and plan their operation, patients are informed about the rationale, design, and conduct of the trial by one of the investigators. Information material is handed out and all pending questions are discussed with the investigator. Patients are asked to provide informed consent to trial participation after due consideration.

### Additional consent provisions for collection and use of participant data and biological specimens {26b}

N/A. There are no planned ancillary studies.

### Interventions

#### Explanation for the choice of comparators {6b}

There is no established medical treatment for the prevention of bleeding and transfusion of PRBCs in major abdominal surgery, which could be used as a comparator. Given the double-blind design of the trial, the comparator thus needs to be a placebo (normal saline solution).

#### Intervention description {11a}

The intervention consists of 1000 mg TXA administered as a bolus over 10 min prior to skin incision and of continuous administration of 125 mg TXA/h from skin incision to skin closure with a maximum dose of 1000 mg. TXA is administered diluted in normal saline with a concentration of 20 mg/ml by using a perfusor via a central or peripheral line.

#### Criteria for discontinuing or modifying allocated interventions {11b}

In case of an urgent medical reason (e.g., intraoperative disseminated bleeding in which a therapeutic use of TXA is deemed indicated), unblinding is possible. In this case, the treating physicians are informed about the patient’s allocation to TXA or placebo and can act according to best individual therapeutic practice including discontinuing or modifying the intervention.

#### Strategies to improve adherence to interventions {11c}

Trial staff is instructed in detail about all interventions. Dosages and modes of administration are clearly displayed in all operation theatres in which trial participants are operated on. Perfusors are used to control the administration and to generate an alarm in case study medication is not properly reaching the participant. Empty vials which contained study medication are collected for monitoring purposes.

#### Relevant concomitant care permitted or prohibited during the trial {11d}

All perioperative and operative procedures are carried out according to clinical standards. Treatment with anticoagulants (e.g., platelet inhibitors, direct oral anticoagulants, vitamin K antagonists) is in principle allowed according to clinical indication. However, all anticoagulants should be paused or bridged with low molecular weight heparin during the perioperative period according to national and local guidelines. Pro-coagulation treatments such as coagulation factors, fresh frozen plasma, platelet transfusions, and Factor XIII substitution can be administered according to the individual judgment of the treating physician.

In case of a thromboembolic event, appropriate treatment should be initiated according to national and local guidelines. This might include medical treatment (e.g., fibrinolysis, anticoagulation) as well as interventional and surgical treatment (e.g., thrombectomy, embolectomy). In this case, an AE/SAE must be reported.

Detailed recommendations for when transfusions should be given are provided to all trial sites based on the cross-sectional guidelines for therapy with blood components and plasma derivates of the German Medical Association [28], thus minimizing heterogeneity across centers with regard to the primary endpoint.

Basic patient blood management is ensured for all participants. Measures include education initiatives and standard operating procedures, massive hemorrhage protocols, coagulation and transfusion algorithms, an online PBM e-learning course for all involved staff, screening for, diagnosis, and treatment of preoperative anemia, intravenous iron if oral iron is not tolerated, postponement of elective surgery until preoperative anemia has been classified and possibly treated, reduction of iatrogenic diagnostic-/surgery-related blood loss, avoiding unnecessary laboratory tests, lower frequency and amount of sampling, cessation and bridging strategies for anticoagulation and antiplatelet therapy, appropriate intraoperative approaches (meticulous hemostasis, minimally invasive surgery, and diathermy dissection). A detailed patient blood management manual will be provided to all trial sites.

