#### Sample size {14}

The sample size calculation is based on the assumption derived from the literature and own hospital data that in the control group (placebo), 30% of participants require intra- or postoperative transfusion of at least one unit of PRBCs [1, 29], and that the intervention (TXA) achieves a relative risk reduction of 33% [18], reducing the probability to 20%. This difference would not only be expected, but also represents a clinically meaningful value. With a type one error (alpha) of 5% and a power of 90%, using a two-sided *χ*^2^ test, this results in 412 participants per group (Software PASS).

Given that the primary endpoint is ascertained at the end of each participant’s hospital stay, virtually no loss to follow-up is expected. Non-compliance, i.e., withdrawal of consent during the study period, i.e., the hospital stay, is expected in 3% of patients, resulting in 425 participants per group to be randomized.

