### Assignment of interventions: allocation

#### Sequence generation {16a}

Participants will be randomized within 24 h prior to surgery in a 1:1 ratio to the TXA or the placebo group. Randomization will be stratified by planned surgical access (open vs. minimally invasive) and planned operation (esophagectomy, gastrectomy, colectomy, rectal resection, pancreatic resection, or hepatectomy). Randomization will be done via an online tool (secuTrial®) generating a randomization number.

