### Statistical methods

#### Statistical methods for primary and secondary outcomes {20a}

The primary endpoint will be compared in the intention-to-treat population between the two study arms with a logistic regression model including the treatment group, and the stratification variables type of operation (esophagectomy, gastrectomy, colectomy, rectal resection, pancreatic resection, hepatectomy) and type of planned surgical access (open, minimally-invasive) as covariates.

The secondary endpoints of postoperative in-hospital complications and mortality will be analyzed similarly. The number of transfused units of PRBCs, estimated intraoperative blood loss, length of hospital stay, operation time, anesthesia time, D-dimer levels, and quality of life will be analyzed using a linear regression model including treatment group, type of operation, and type of surgical access as covariates. In case of heavy skewness in the outcome data, the outcome variables will be transformed to reduce skewness. All results for secondary outcomes will be interpreted in an exploratory sense. Dichotomous outcomes will be reported as absolute and relative frequencies and continuous variables by means, medians, standard deviations, and ranges. Time to transfusion will be compared between both arms using time-to-event analysis.

A safety analysis will be carried out by comparing the frequency of all adverse events and adverse events attributed to the intervention between the two study arms. Patients with a history of thromboembolic events will be analyzed as a subgroup of special interest.

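### The protocol treats center differences in transfusion as a concern, but the primary model does not adjust for center; this costs a little precision and causes no bias

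*Protocol article*

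**What the plan says.** Under Study setting {9}, the protocol article states: "The study is conducted at eleven academic hospitals in Germany". Outcomes {12} makes the primary endpoint the need for at least one unit of packed red blood cells.

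Relevant concomitant care {11d} gives all sites detailed recommendations on when to transfuse, drawn from a national guideline, "thus minimizing heterogeneity across centers with regard to the primary endpoint". The same section provides patient blood management for every participant, including standard operating procedures, transfusion algorithms, staff e-learning and a manual. It describes no binding transfusion trigger.

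On allocation, Sequence generation {16a} says: "Randomization will be stratified by planned surgical access (open vs. minimally invasive) and planned operation". The primary analysis under Statistical methods {20a} is "a logistic regression model including the treatment group, and the stratification variables type of operation", together with planned surgical access. Center is in neither list. Both lists are explicit, so this choice is made in the article and not left open for a later document.

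**The concern.** The article names center as a source of variation in the primary endpoint, then deals with it through conduct alone. Guidance and training can narrow differences in transfusion habit, but they need not remove them. Surgical technique and case mix within an operation type may also differ between hospitals.

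Center is known for every patient at randomization. If it predicts transfusion, leaving it out of the model has two effects. Chance differences between the arms in center composition stay in the treatment estimate, and some explainable variation is treated as noise. What is at stake is precision, not validity.

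**Working it through.** **Inputs from the article.** Sample size {14}: placebo risk 30%, tranexamic acid risk 20%, two-sided alpha 5%, power 90%, 412 per group, 3% non-compliance, 425 randomized per group. Study setting {9}: 11 centers. Sequence generation {16a}: 2 access types × 6 operations = 12 strata.

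**1. Reproduce the plan's sample size.** With mean risk 0.25 and difference 0.10:

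n = [1.960·√(2·0.25·0.75) + 1.2816·√(0.30·0.70 + 0.20·0.80)]² / 0.10² = (1.2002 + 0.7795)² / 0.01 ≈ 392.

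Continuity correction: (n/4)·[1 + √(1 + 4/(n·0.10))]² = 98.0 × 2.0498² ≈ 412. Then 412/0.97 = 424.7, so 425. Both stated figures reproduce. Without the correction, 412 per group gives 91.4% power, which leaves a small margin above 90%.

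**2. Size of chance center imbalance.** An average center has 850/11 ≈ 77 patients. Under simple 1:1 allocation within a center, the binomial chance of a split worse than 60:40 is 6.8% with 77 patients and 20.0% with 30.

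For assumed between-center log-odds standard deviations (SD) of 0.3 to 1.0, simulation puts the random error that this adds to the risk difference at an SD of about 0.4 to 1.2 percentage points. For comparison, the ordinary standard error of the risk difference is √[(0.21 + 0.16)/412] = 3.0 points. The imbalance is therefore roughly (0.4/3.0)² ≈ 2% to (1.2/3.0)² = 16% of that variance.

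**3. Power with and without center.** The simulation used 824 patients, 11 centers of unequal size, blocks of 4 within the 12 strata, overall risks held at 30% and 20%, and normal center effects on the log-odds scale. The article's model was compared with the same model plus fixed center effects. Run 1 had 1,500 trials per setting (Monte Carlo standard error about 0.7 points). Run 2 is a separate simulation of the same stratified design and model. Center sizes, operation mix, access split, block size and the between-center SD are all assumptions.

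| Assumed SD | Run 1: article's model | Run 1: plus center | Change | Run 2: article's model | Run 2: plus center | Change |
|---|---|---|---|---|---|---|
| 0 | 91.4% | 91.0% | −0.4 | 93.6% | 93.1% | −0.5 |
| 0.3 | 92.8% | 93.0% | +0.2 | – | – | – |
| 0.5 | 91.8% | 93.3% | +1.5 | 92.4% | 92.8% | +0.4 |
| 0.8 | 92.2% | 94.8% | +2.6 | 92.4% | 94.6% | +2.2 |
| 1.0 | 92.5% | 94.9% | +2.5 | 91.9% | 94.7% | +2.8 |

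Changes are taken before rounding where unrounded values are available. The runs differ in level by up to about 2 points, so the changes are the more reliable reading.

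To show what the SDs mean: at the model intercept, where placebo risk is 34% with no center effect, the 10th to 90th percentile of center risk is 26–43% at SD 0.3, 21–49% at 0.5, 14–57% at 0.8 and 11–62% at 1.0.

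**4. Type I error.** In run 1 the article's model rejected a true null in 4.5% to 5.6% of trials across all SDs. The Monte Carlo standard error here is √(0.05·0.95/1500) ≈ 0.6 points, so this is consistent with 5%.

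**5. Change in the odds ratio.** At SD 0.5 the mean log odds ratio moves from −0.563 to −0.594 (odds ratio 0.57 to 0.55). At SD 1.0 it moves from −0.576 to −0.667 (0.56 to 0.51).

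**6. Could the strata take center instead?** 12 × 11 = 132 cells, and 850/132 ≈ 6.4 patients per cell.

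**The case against.** The strongest reply is that the plan is coherent as it stands. It adjusts for exactly the factors it stratifies on, and those factors already carry part of the case mix. Treating physicians are blinded (Who will be blinded {17a}), so transfusion habit cannot favor an arm. The standardization in {11d} goes well beyond recommendations. The larger power gains need center differences that the article does not report and that its conduct measures are meant to reduce. All of this stands and limits the point to an optional improvement.

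The strata are also defensible, since adding center would leave about 6 patients per cell. They are not criticized here.

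Three stronger readings are tempting and not supported:

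- A reader might infer that each transfusion is left to the individual physician. The wording in {11d} about individual judgment concerns pro-coagulation treatments, not red cells. That red-cell decisions vary by hospital is a fair inference, not a statement in the article.
- A reader might infer that power falls below 90%. A simulation specified without operation and access terms gave 89.8% without center and 93.9% with it at SD 1.0. Neither that level nor that 4-point gain recurs under the article's stratified design and model.
- A reader might infer that the odds ratio nearer to 1 without center is a bias. It is non-collapsibility: the model without center estimates a less conditional quantity.

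What the reply does not answer is why a factor that the article itself links to the primary endpoint, known at baseline and nearly free to include, should stay out of the model.

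**Conclusion.** The point holds as a modest, optional gain in precision. Center is in neither the strata nor the primary model, although the article treats it as relevant to the endpoint. The omission causes no bias and no type I error inflation. The article's model had at least 91.4% power in every scenario simulated under its own design.

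Adding center gains about 0 to 3 points of power if the between-center SD is 0.3 to 1.0. If there is no center effect it costs at most about half a point, within simulation error. The range rests on an assumed SD and on assumed center sizes and operation mix.

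It would go too far to say that a center term would show whether the treatment effect is shared across hospitals. A main effect or random intercept does not show that; treatment-by-center estimates would. Such summaries, and what the case report form records about each transfusion, may be settled in documents not shown, so they are not part of this point.

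**What to change.** Leave the randomization unchanged. Before unblinding, amend Statistical methods {20a} so that the primary logistic model contains treatment, operation, planned access and center, and do likewise in the secondary models.

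Center can enter in one of two ways, chosen in advance:

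- **Random intercept.** This needs no pooling and copes better with small centers, with centers added later (the steering committee may add them, {5d}), and with rare outcomes such as mortality.
- **Fixed effects.** This needs a pre-stated pooling rule for very small centers, based on the number randomized and not on outcomes.

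Costs: up to 10 degrees of freedom, against 412 × 0.30 + 412 × 0.20 ≈ 206 expected events; an odds ratio that is conditional on center and should be labeled so; and a protocol or analysis-plan modification. Recruitment began in June 2024, and under {25} a substantial modification needs approval before use. No new data are needed, and the sample size stays at 412 evaluable and 425 randomized per group.
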